### Population and sampling procedures

The target sample for each intervention 'arm' as well as for the control 'arm' is 250 pupils, i.e. 1,000 subjects in each participating country (totaling 11,000 subjects overall).

In each study site, a catchment area is identified and a list of eligible schools generated. Eligible schools are categorized by size as (1) **small **(less than or equal to the median number of pupils in all schools in the study catchment area or region) and (2) **large **(greater than the median number of pupils in all schools in the study catchment area or region). Every class in each school selected (regardless of size) where 15-year-old pupils make up a majority is surveyed. This age group is selected because of its risk propensity and the feasibility of performing 12-month follow-ups. Schools are randomized on the basis of their size category and sequentially assigned to respective intervention and control arms, comprising both large and small schools. The remaining large and small schools are then sequentially numbered.

To avoid contamination and confounding, only one type of intervention is performed in each school. Given the insufficient evidence of effectiveness of the interventions, equipoise can be assumed so that no institution or group will be put at (dis)advantage systematically. Schools are only aware of the respective intervention arm implemented at their facility, i.e. pupils are not informed of the other types of intervention performed in other schools. The effect that information could eventually spread through informal suggestions can be neglected; in case this becomes a topic, project members would apply a strategy to openly give appropriate additional information. A coordinator is assigned to each intervention arm and its implementation. Coordinators in the respective schools for each arm are instructed only on how to implement their own intervention arm, and have no prior experience of the procedures for the other interventions. Informed consent to participate in the study is obtained from all the adolescents and their parents.

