### Inclusion and exclusion criteria

Schools and adolescents in the study areas are eligible to participate if they meet all the following criteria:

(1) the school authority agrees to participate;

(2) the adolescents attend non-specialist public schools;

(3) school contains at least 40 pupils aged 15;

(4) school has more than two (3+) teachers for pupils aged 15;

(5) no more than 60% of pupils are of either sex;

(6) informed consent from parents and pupils is obtained.

If the school-based adolescents meet the following exclusion criteria, they are ineligible to participate:

(1) the school authority refuses to participate;

(2) the adolescents attend a specialist and/or independent or private school;

(3) the adolescents attend single-sex schools;

(4) a school has fewer than 40 pupils aged 15;

(5) the parents of pupils in a participating school, or the pupils themselves, have refused to sign the consent document.

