### Data analysis

The SEYLE project generates a total sample of 11,000 European adolescents, with 8,250 (750 per site) receiving one or other of the three interventions being tested. The control arm contributes 2,750 adolescents (250 per site) to the total sample.

Power calculations adhere to the widely accepted proposals made by Cohen (1988) [57] for detection of small, medium and large effects. For all outcome measures, the sample size gives the study more than 80% statistical power to detect medium effects within the individual centers and small effects at the aggregate level of centers. Overall, the SEYLE intervention project is expected to show medium effect changes.

The SEYLE study sample potentially exceeds the sample size requirements in order to detect statistically significant changes. This will ensure the required statistical power, taking into account the possibility of some center recruiting fewer pupils than expected, attrition rates at follow-up and missing data. An initial stage of statistical analysis involves examining the consistency of psychometric properties across sites of the measures used in the SEYLE study. Reliability analysis is performed on the relevant data from each participating center. The suitability of continuous variables for parametric tests is assessed.

In cases where the diagnostics indicate that the reliability of the parametric tests may be significantly undermined, the appropriate non-parametric test is carried out. These include the Mann-Whitney test, the Kruskal-Wallis test, the Wilcoxon test and Friedman's ANOVA. Comparisons between study arms in relation to dichotomous and polychotomous variables are initially made using Fisher's exact test and chi-square tests, as appropriate. Logistic regression compares the intervention arms to the control arm in relation to the risk of an event of interest occurring in the follow-up period. The odds ratio, with its 95% confidence interval, is used as the measure of relative risk. An adjusted odds ratio is produced from multivariate logistic regression models, which include relevant covariates. Statistical analyses are carried out at the level of the individual centers and at the aggregate level. Variation in the experimental effects is examined across the 11 participating centers.

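### Schools are randomised, but every between-arm test named treats pupils as independent, so p-values are too small and confidence intervals too narrow for any positive school ICC

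*Protocol article*

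**What the plan says.** **Design (Population and sampling procedures).** The school is the randomised unit: "Schools are randomized on the basis of their size category and sequentially assigned to respective intervention and control arms". The same section adds that "only one type of intervention is performed in each school". Delivery also works through the school or classroom: staff training, lessons and role-play, and posters.

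**Sizes.** Per country, "The target sample for each intervention 'arm' as well as for the control 'arm' is 250 pupils". In aggregate, "The control arm contributes 2,750 adolescents (250 per site) to the total sample". The number of schools per arm is not given. The only guide to school size is the eligibility criterion "school contains at least 40 pupils aged 15". Arms are to include both small and large schools, which I read as at least two schools per arm in each country.

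**Analysis (Data analysis).** For categorical outcomes: "Comparisons between study arms in relation to dichotomous and polychotomous variables are initially made using Fisher's exact test and chi-square tests". For continuous outcomes the article plans unnamed parametric tests, with Mann-Whitney, Kruskal-Wallis, Wilcoxon and Friedman as fallbacks. Logistic regression then compares each intervention arm with control: "The odds ratio, with its 95% confidence interval, is used as the measure of relative risk". Covariates are mentioned but not listed. Analyses run per centre and pooled, and variation of effects is examined across the 11 centres. Clustering within schools is not mentioned anywhere in the article.

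**Power (Data analysis).** The sample is said to give "more than 80% statistical power to detect medium effects within the individual centers and small effects at the aggregate level of centers".

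**The concern.** Pupils in one school share teachers, peers, neighbourhood and, in this trial, the intervention. Their outcomes tend to resemble one another, and arm is constant within a school. The information about an arm therefore depends on the number of schools as well as the number of pupils. A pupil-level Fisher, chi-square, Mann-Whitney or Kruskal-Wallis test, or a logistic regression with the usual model-based variance, leaves out the between-school part of the variance.

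Analysing by centre does not repair this, because country is a level above the school. Nor does adding school as an ordinary covariate: schools are nested in arms, so school indicators would absorb the arm effect.

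The trial is meant to recommend school-based suicide-prevention strategies. Followed as written, chance differences between schools could be reported as benefit or harm too often, over many outcomes, in single centres and in the pooled data.

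**Working it through.** **Step 1. Reproduce the stated power, with independent pupils.** Inputs: 250 per arm per centre and 2,750 (= 11 × 250) per arm in aggregate, from the article. Assumed: two-sided 5% level (from the 95% interval) and standardised differences of 0.5 for medium and 0.2 for small (the article cites Cohen's convention without printing values). Power is 99.99% for 0.5 with 250 per arm, and above 99.99% for 0.2 with 2,750 per arm. Only 63 and 393 per arm are needed for 80%. The statement reproduces if pupils are independent.

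**Step 2. Effect of clustering on the named tests.** For *m* analysed pupils per school:

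- design effect DE = 1 + (*m* − 1) × ICC
- true standard error = √DE × the pupil-level standard error
- true type I error of a nominal 5% test = 2 × [1 − Φ(1.96 / √DE)]

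ICC and *m* are assumptions. I take *m* = 40 (the eligibility floor), 62.5 (250/4, four schools per arm) and 125 (250/2, two schools per arm).

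| *m* | ICC | DE | √DE | True type I error |
|---|---|---|---|---|
| 40 | 0.005 | 1.20 | 1.09 | 7.3% |
| 40 | 0.01 | 1.39 | 1.18 | 9.6% |
| 40 | 0.02 | 1.78 | 1.33 | 14.2% |
| 40 | 0.05 | 2.95 | 1.72 | 25.4% |
| 62.5 | 0.01 | 1.61 | 1.27 | 12.3% |
| 62.5 | 0.02 | 2.23 | 1.49 | 18.9% |
| 62.5 | 0.05 | 4.08 | 2.02 | 33.2% |
| 125 | 0.01 | 2.24 | 1.50 | 19.0% |
| 125 | 0.02 | 3.48 | 1.87 | 29.3% |
| 125 | 0.05 | 7.20 | 2.68 | 46.5% |

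Example: *m* = 62.5, ICC 0.02 gives DE = 1 + 61.5 × 0.02 = 2.23, and 1.96/√2.23 = 1.31, which is a two-sided 18.9%.

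A beta-binomial simulation of the pupil-level two-proportion test (20,000 runs per cell, event rates 4% and 20%, about 42, 62 and 125 pupils per school) agrees, mostly within one percentage point; the largest gap is about 2.5 points, at *m* = 125 and ICC 0.05. The inflation is about the same per centre and in aggregate, since DE depends on pupils per school and not on the total. The simulation checks the formula, not the assumed inputs.

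**Step 3. Interval widths.** In aggregate, with many schools, the correct interval is √DE times the planned one: about 1.2 to 2.7 times as wide for ICC 0.01 to 0.05. Within one centre, with *k* schools per arm, the degrees of freedom are 2(*k* − 1) and the ratio is (t / 1.96) × √DE:

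- *k* = 6 (*m* = 41.7), ICC 0.01: t with 10 df = 2.228, √DE = 1.186, ratio 1.35
- *k* = 2 (*m* = 125), ICC 0.05: t with 2 df = 4.303, √DE = 2.683, ratio 5.9

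**Step 4. What a valid analysis does to power.** From DE alone (normal quantiles), the power statement fails per centre only when DE exceeds about 4.0 (250/63), and in aggregate only when it exceeds about 7.0 (2,750/393). With a school-level t-test inside one centre and a standardised difference of 0.5, power is about 52% (ICC 0.01) and 39% (ICC 0.02) with two schools per arm, and about 95% and 87% with four.

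**The case against.** The case for the article has four parts.

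- **It is condensed and an analysis plan may exist.** Neither the variance method nor the covariates of the logistic model are given, so for that model the criticism rests partly on silence. This stands as a limit: the claim concerns the between-arm methods as described. It does not remove the point, because Fisher, chi-square, Mann-Whitney and Kruskal-Wallis are named, and in their standard form they cannot carry a school effect.
- **Not every listed test is at fault.** Wilcoxon (if signed-rank) and Friedman handle repeated measures on a pupil, not comparisons between arms, and the parametric tests are unnamed. This stands, and these methods are left out of the point. The article also calls the Fisher and chi-square comparisons initial; used only as description they would do no harm, but it does not limit them to that.
- **The size is not in the documents.** A reader might infer that type I error is certainly inflated several-fold. The documents do not support that. The 40-pupil floor counts 15-year-olds in the school, not analysed pupils, and consent refusal and attrition can take the analysed number lower. At an assumed 25 per school the error is 7.8% at ICC 0.01 and 10.7% at 0.02. The 47% figure belongs to one corner: two schools per arm with ICC 0.05.
- **The trial is large.** A reader might infer that the power claim is refuted. It is not: on the design effect alone it survives much of the range. But a large sample does not cure false positives. Pooling averages over more schools, so chance school differences *could* be misreported at the inflated rate; it does not follow that they *would* be.

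**Conclusion.** The point holds for the between-arm methods that are named. The article randomises schools and then specifies comparisons that ignore them, so this is a method fixed wrongly and not a detail left to another document. The direction is certain for any positive school ICC: p-values too small and intervals too narrow, at both levels of analysis.

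The size is conditional. For ICC 0.01 to 0.05 and 40 to 125 analysed pupils per school, the inflation is about two-fold to nine-fold; at ICC 0.005 with 40 pupils it is about 1.5-fold (7.3/5). Centre-level results are the most exposed, because a country may have only a handful of schools per arm.

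**What to change.** - **Main inference:** mixed-effects logistic or linear regression with a random intercept for school and fixed effects for arm, country and school-size category. Alternatively, GEE or a cluster-robust variance with a small-sample correction.
- **Single centres:** school-level summaries with degrees of freedom based on schools, or country estimates from the pooled model without separate significance tests.
- **Fisher, chi-square and rank tests between arms:** keep as descriptive only.
- **Power:** recheck and restate the within-centre and aggregate claims, giving the assumed ICC, the number of schools per arm and the analysed pupils per school.

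**Cost.** The analysis wording changes and no further pupils are needed for valid inference. School must be linked to each record; the Research Ethics section mentions only a pupil code, so this should be confirmed, though allocation by school implies that the link exists. The intervals become wider, and the within-centre power claim may have to be weakened or withdrawn where there are few schools per arm.

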**Substance abuse**	**Tobacco**	Tobacco Use (lifetime measure)	'Yes' is the response given to tobacco use, **and **2 cigarettes per day or more for tobacco consumption frequency.
			
		Tobacco Consumption Frequency	
	
	**Alcohol**	Alcohol Consumption Frequency (12-month measure)	2 times per week or more
		
		Alcohol Consumption Amount (12-month measure)	3 or more drinks in a typical drinking day
		
		Alcohol Intoxication (lifetime measure)	3 times or more
		
		Alcohol Hangover (lifetime measure)	3 times or more
	
	**Illegal drugs**	Illicit Drug Consumption (lifetime measure)	3 times or more

**Exposure to media**		Media Exposure Frequency	Option 4, 5 or 6 is ticked, i.e. a pupil spends at least 'five to six hours per day' watching television, playing computer games etc.

**Social relationships**		Loneliness Frequency (12-month measure)	Option 4 ('most of the time') or 5 ('always') is checked.

**Bullying**		Peer Victimization (12-month measure)	The sum of ≥ 5 is obtained. All response options must therefore be added.

***School attendance***		Truancy (2-week measure)	Option 3, 4 or 5 is ticked, i.e. respondents have missed three or more days of school or class without permission.

The time period for the active intervention in the Professional Screening arm is 4-week duration.

All pupils with a predetermined cut-off for depression, anxiety, phobia, alcoholism, substance abuse, non-suicidal self-injury (NSSI) and suicidality are referred for professional treatment. Pupils with social problems are referred to an appropriate non-clinical healthy-lifestyle group.

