### Outcome measures

Outcome variables that are assessed in the project include well-being, depression, anxiety, emotional and conduct problems, coping, self-destructive and addictive behaviors, values, and lifestyles. Table 3 illustrates the outcome variables and the corresponding assessment tools utilized to measure them.

**Table 3 T3:** Correspondence between questionnaire measures and study outcomes

Tool for measurement	Outcome variables
WHO-5	General well-being

Beck Depression Inventory (BDI)	Depression

Paykel Suicide Scale (PSS)	Suicidal behavior

Global School-Based Pupil Health Survey (GSHS)	Alcohol use and abuse
	
	Drug use and abuse
	
	Eating habits
	
	BMI
	
	Physical activity
	
	Sexual habits
	
	Tobacco use
	
	Violent behaviors
	
	Risky behaviors

Strengths and Difficulties Questionnaire (SDQ)	Emotional symptoms
	
	Conduct problems
	
	Hyperactivity/inattention
	
	Peer relationship problems
	
	Pro-social behavior

European Values Study Questionnaire (EVS)	Values (religion, family, marriage, work, friendship)

Specific SEYLE questions	Coping
	
	General child health
	
	Peer relations
	
	Child-parent relations
	
	Stigma and discrimination
	
	Future outlook

Deliberate Self Harm Inventory (DSHI)	Self-harm behavior

Young's Diagnostic Questionnaire (YDQ) for Internet Addiction	Internet addictive behavior

Another outcome variable is pupil referrals, i.e. the total number of referrals inclusive all emergency cases identified during the baseline evaluation, and treatment outcomes. For data collection, SEYLE has developed a systematic method of recording and monitoring all referrals and obtaining feedback on their appropriateness. Pupils are asked whether they have been referred and to whom, what kinds of treatment they have received (medication, psychotherapy, both or neither etc.) and for how long. Phone calls are performed with pupils who do not participate in the follow-up evaluations, and, where possible, facilitators maintain contact with the pupils' parents. In cases, where parents or family represent a source of concern in the perception of the pupil or staff member, contacts will be handled in a particularly careful manner [56].

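### The plan takes the odds ratio as the relative risk with no rare-event condition, which exaggerates effects for any outcome that is not rare

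*Protocol article*

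**What the plan says.** The Data analysis section of the protocol article defines the target of the event analysis as a risk: "Logistic regression compares the intervention arms to the control arm in relation to the risk of an event of interest occurring in the follow-up period". Its next sentence names the effect measure: "The odds ratio, with its 95% confidence interval, is used as the measure of relative risk". The one after adds covariate adjustment: "An adjusted odds ratio is produced from multivariate logistic regression models, which include relevant covariates". No sentence limits this reading to rare events or converts the odds ratio to a risk ratio.

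The events are not named there. The Outcome measures section describes a wide field, which includes "self-destructive and addictive behaviors, values, and lifestyles". Its Table 3 places suicidal behaviour beside alcohol, drug and tobacco use, eating and sexual habits, and physical activity. Table 2, under III. Professional Screening, shows the kind of threshold that could make such an item binary, for example "3 or more drinks in a typical drinking day". That is a screening cut-off and not a stated outcome definition. No event rate is given for any outcome.

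**The concern.** The quantity of interest is a ratio of risks, the quantity estimated is a ratio of odds, and the plan treats the second as the first. This is close to true only when the event is rare in both arms. The plan covers suicidal behaviour, which may be rare, and drinking or smoking among 15-year-olds, which may not be.

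At stake is how large the reported effects appear. Someone who follows the sentence as written would report one minus the odds ratio as the relative reduction in risk. Away from the null this always errs towards a larger effect, for benefit and for harm alike, and the error grows with the control risk. A programme's effect on a common behaviour would be overstated more than its effect on a rare one. The trial means to use its results to recommend programmes to schools.

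**Working it through.** **Inputs.** The effect measure and its label come from Data analysis. Group sizes are 250 pupils per arm per country (Population and sampling procedures) and 2,750 in the control arm overall (Data analysis). Control risks *p* of 2% to 50% are assumed, because the article gives none. The effects used (risk ratio 0.70; odds ratios 0.70 and 2.0) are illustrations, not the plan's figures.

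**1. The plan's own figure.** No figure is attached to the odds-ratio sentence. The one design figure is power above 80% for medium effects within a centre and small effects overall. Take standardised effects of 0.5 and 0.2 as the usual meaning, two-sided alpha 0.05, and pupils as independent:

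- Within a centre: 0.5 × √(250/2) − 1.96 = 5.590 − 1.96 = 3.63, so power is 0.9999.
- Overall: 0.2 × √(2750/2) − 1.96 = 7.416 − 1.96 = 5.46, so power is above 0.9999.

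The statement is reproduced on those terms and does not depend on the choice of effect measure.

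**2. From a true risk ratio to the odds ratio.** OR = RR(1 − *p*) / (1 − RR·*p*). With RR = 0.70:

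| Control risk (assumed) | Calculation | OR | Reduction if OR is read as RR | True reduction |
|---|---|---|---|---|
| 2% | 0.686/0.986 | 0.696 | 30.4% | 30% |
| 10% | 0.630/0.930 | 0.677 | 32.3% | 30% |
| 20% | 0.560/0.860 | 0.651 | 34.9% | 30% |
| 30% | 0.490/0.790 | 0.620 | 38.0% | 30% |
| 50% | 0.350/0.650 | 0.538 | 46.2% | 30% |

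**3. From a reported odds ratio to the risk ratio.** RR = OR / (1 − *p* + *p*·OR).

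| Control risk (assumed) | RR when OR = 0.70 | RR when OR = 2.0 |
|---|---|---|
| 2% | 0.704 | 1.961 |
| 10% | 0.722 | 1.818 |
| 20% | 0.745 | 1.667 |
| 30% | 0.769 | 1.538 |
| 50% | 0.824 | 1.333 |

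An odds ratio of 0.70 read as a 30% reduction is really 29.6% at 2% control risk, 25.5% at 20% and 17.6% at 50%. An odds ratio of 2.0 read as a doubling is really an increase of 96% at 2%, 67% at 20% and 33% at 50%.

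**4. The same error in absolute terms.** At 50% control risk, a risk ratio of 0.70 takes the risk to 35%, a fall of 15 percentage points. Applying the odds ratio of 0.538 as if it were a risk ratio gives 0.538 × 50% = 26.9%, an apparent fall of 23.1 points. At 2% the corresponding falls are 0.60 and 0.61 points (2% × 0.304 = 0.61%).

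**The case against.** The strongest defence is that this is a matter of wording. The odds ratio is a legitimate measure, it will be printed as an odds ratio, and relative risk may be meant loosely as any relative effect measure. Test results, intervals on the odds-ratio scale and power do not change. With no prevalence in the article, a common outcome is an assumption, and at 2% to 10% the distortion is nil to small. All of this is correct and sets the weight of the point. It does not rescue the sentence, which follows directly on one about risk and carries no rare-event condition. Nor is this a detail left to an unseen analysis plan, since the article states how the measure is to be used.

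A reader might infer more, and the documents do not support it:

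- **That odds ratios cannot be compared across outcomes or countries.** They can be compared with one another. The article plans a between-centre comparison ("Variation in the experimental effects is examined across the 11 participating centers") and does not state its scale. The risk ratio is no more constant: a fixed odds ratio of 0.50 is a risk ratio of 0.505 at 2% and 0.667 at 50%.
- **That non-collapsibility is an error here.** Adjusted and unadjusted odds ratios do differ without confounding. With an assumed prognostic covariate of standard deviation 1 on the logit scale, a conditional 0.50 is a marginal 0.507 at 2% control risk and 0.563 at 50%. But that is a property of every logistic model, the article labels the adjusted value as an adjusted odds ratio, and it nowhere says that the gap measures confounding.
- **That the cost-effectiveness analysis is undermined.** The objective is named, but nothing says that odds ratios feed it.
- **That every dichotomous outcome is affected.** Those variables are first compared by Fisher's exact or chi-square tests. Logistic regression is for events of interest, which are not listed.

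**Conclusion.** The concern holds as an error of labelling and interpretation. As written, the plan would have effects on non-rare events reported as larger relative changes in risk than they are. For a true 30% reduction, the overstatement is under half a percentage point at 2% control risk, about 5 points at 20%, 8 points at 30% and 16 points at 50%. These sizes rest on assumed control risks. Whether any given outcome falls in the upper range cannot be settled from the article, though alcohol and tobacco use may. For rare events such as suicide attempts may prove to be, the sentence does little harm. Nothing in the tests, the odds-ratio intervals or the stated power is invalidated. The clustering of pupils within schools is a separate matter and adds no weight here.

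**What to change.** In Data analysis, remove the clause that makes the odds ratio the measure of relative risk, and call odds ratios odds ratios throughout. For event outcomes, also report the standardised (marginal) risk ratio and risk difference with 95% confidence intervals. These come from the same logistic model: predict each pupil's risk under intervention and under control, average each set over the sample, and take the ratio and the difference, with intervals by the delta method or bootstrap. Suggested wording: Logistic regression yields odds ratios with 95% confidence intervals; for each event outcome, standardised risk ratios and risk differences with 95% confidence intervals are derived from the same model, and statements about relative risk refer to the risk ratio.

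The cost is one post-estimation step per model and a slightly longer results table. No new data and no change of design are needed. Some relative effects on common behaviours will look smaller than the odds ratios would suggest.

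### The between-arm tests named for the aggregate analysis carry no centre term: harmless at the planned equal arms, but open to country differences if realised arm sizes differ within countries

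*Protocol article*

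**What the plan says.** In Population and sampling procedures the randomisation is organised by site: "In each study site, a catchment area is identified and a list of eligible schools generated". Schools are classed as small or large against the median of their own catchment area, and "Schools are randomized on the basis of their size category and sequentially assigned to respective intervention and control arms". The size target is the same everywhere: "The target sample for each intervention 'arm' as well as for the control 'arm' is 250 pupils, i.e. 1,000 subjects in each participating country". Every class with a majority of 15-year-olds in a selected school is surveyed.

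In Data analysis, for categorical outcomes, "Comparisons between study arms in relation to dichotomous and polychotomous variables are initially made using Fisher's exact test and chi-square tests, as appropriate". Where diagnostics count against parametric tests, non-parametric ones replace them: "These include the Mann-Whitney test, the Kruskal-Wallis test, the Wilcoxon test and Friedman's ANOVA". Logistic regression then compares each intervention arm with control, first unadjusted and then with covariates that are not listed. On the level of analysis: "Statistical analyses are carried out at the level of the individual centers and at the aggregate level". Variation of the effects across the 11 centres is also examined. The section allows for centres recruiting too few pupils, for attrition and for missing data, without giving rates.

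**The concern.** Because schools are listed and size-classed within each site, centre is a stratum of the randomisation, and the question is whether arms differ within centres. A pooled chi-square, Fisher, Mann-Whitney or Kruskal-Wallis test asks something else: whether the pooled outcome distribution is the same in each arm. The two questions coincide when each country supplies the same share of pupils to every arm. When the shares differ, an arm with more pupils from a high-prevalence country looks worse with no programme effect anywhere.

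At stake are spurious or masked effects in the aggregate comparison, across the long outcome list in Table 3. The problem is distinct from correlation of pupils within schools. It would arise even if pupils within a country were fully independent.

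**Working it through.** **1. The plan's own figures.** 250 × 11 = 2,750 controls ("The control arm contributes 2,750 adolescents (250 per site) to the total sample"); 750 × 11 = 8,250 in the active arms ("8,250 (750 per site) receiving one or other of the three interventions being tested"); 2,750 + 8,250 = 11,000. The figures agree, and by plan each country supplies 250/2,750 = 1/11 of every arm.

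**2. What the pooled test sees.** Let p_c be the outcome rate in country c, the same in both arms (no arm effect), and w_ac the share of arm a that comes from country c. The expected pooled difference is D = Σ p_c (w_1c − w_0c). With all shares equal to 1/11, D = 0.

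**3. Size of the error.** Let arm sizes vary independently around 250 with CV v. Let p̄ be the mean and S² the variance of the country rates.
- Variance of D from country mix: about 2v²S²/11.
- Sampling variance within countries: about 2[p̄(1−p̄) − S²]/2,750.
- Variance the pooled test assumes: 2p̄(1−p̄)/2,750.

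The ratio of true to assumed variance is R = 1 + S²(250v² − 1)/[p̄(1−p̄)], and the rejection rate is 2Φ(−1.96/√R). The pooled test is conservative while v < 1/√250 = 6.3% and over-rejects above that.

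Example, country rates evenly spaced from 5% to 30%: p̄ = 0.175, p̄(1−p̄) = 0.1444, S² = 0.025² × (11² − 1)/12 = 0.00625, so S²/[p̄(1−p̄)] = 0.0433.
- v = 0: R = 1 − 0.0433 = 0.957, error 4.5%.
- v = 10%: R = 1 + 0.0433 × 1.5 = 1.065, error 5.8%.
- v = 20%: R = 1 + 0.0433 × 9 = 1.390, error 9.6%.
- v = 30%: R = 1 + 0.0433 × 21.5 = 1.931, error 15.8%.

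**4. Simulation.** 40,000 runs per setting, two arms, 11 countries, no arm effect, no school clustering. Country rates and v are assumptions; the article gives neither. Pooled chi-square rejection rate at nominal 5%:

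| Country rates (assumed) | v = 0 | 10% | 20% | 30% |
|---|---|---|---|---|
| 2–6% | 4.9% | 5.2% | 5.3% | 6.0% |
| 2–10% | 4.9% | 5.3% | 6.1% | 8.3% |
| 5–30% | 4.5% | 5.8% | 9.6% | 16.0% |
| 10–50% | 4.0% | 6.2% | 13.2% | 23.4% |
| mean 25%, SD 5 points | 4.9% | 5.4% | 6.3% | 8.1% |
| mean 25%, SD 10 points | 4.5% | 6.0% | 10.4% | 16.8% |
| mean 25%, SD 15 points | 4.0% | 6.7% | 15.2% | 26.3% |

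The centre-stratified Cochran-Mantel-Haenszel test stayed at 4.8–5.2% throughout. Pooled Mann-Whitney (2,000 runs), with a between-country SD of 0.2 or 0.4 within-country SDs, gave 4.1% and 3.5% at equal arms, 9.0% and 19.5% at v = 20%, and 14.9% and 32.5% at v = 30%.

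**5. Shortfall shared by the arms.** If centres under-recruit equally in both arms (country rates 5–30%), the pooled test gives 4.4% and the stratified one 4.9%. Only imbalance between arms within a country does harm.

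**6. Which v is plausible.** The article gives only a floor of 40 pupils aged 15 per school. If three or four schools fill an arm and eligible numbers are uniform on 40–120, v is 17% or 14%. Size stratification lowers this. With two small and two large schools per arm, split at the midpoint:
- Range 40–120: the SD of the sum is 2 × 40/√12 = 23.1 on a mean of 320, so v = 7%.
- Range 40–200: 2 × 80/√12 = 46.2 on a mean of 480, so v = 10%.

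Both are before refusal and attrition, and both means lie above the 250 target.

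**The case against.** The strongest reply is that the plan is balanced. With 250 pupils per arm in each country, no effect within centres implies no pooled difference, and the tests err slightly on the safe side. This stands. A reader might infer that the arms differ in country composition by design, or that they are bound to differ in the end. The documents support neither. A shortfall at a centre need not fall on one arm, and placing both small and large schools in each arm limits imbalance. Whole-school allocation, surveying every eligible class and attrition make unequal arms plausible, not certain.

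A reader might also infer that the plan ignores centre altogether. It does not say so. Chi-square and Fisher tests are only the initial step, rank tests are a fallback, the adjusted logistic models could include centre, and variation across centres is examined. That too stands, but it does not remove the point. The named tests have no centre term in their ordinary form, centre enters the logistic models only if someone chooses it, and examining variation in effects does not repair a pooled test.

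Finally, an ordinary pupil-level stratified test still treats pupils as independent although schools are randomised. This is right, and it shapes the fix. The near-5% error of the stratified test above holds only because school clustering was set to zero.

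**Conclusion.** The point holds as a weakness in the stated method that costs nothing to remove; the plan's balanced allocation is not at fault. At equal arms the pooled tests run at about 4–5%. With unequal arms within countries and an outcome averaging 25%, pooled chi-square error is about 5–6% at v = 10% (6.7% at the widest country spread), 6–15% at 20% and 8–26% at 30%. It is smaller for rare outcomes: with country rates of 2–6% it is 6.0% even at v = 30%. Mann-Whitney can do worse where countries differ strongly.

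These figures rest on assumed arm-size variation and country spread, on independent variation between arms, and on no clustering by school. If arm sizes vary by only 7–10%, as the size-stratified example suggests, inflation is slight. The 30% column shows what substantial arm-specific loss could do and is not a forecast.

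**What to change.** State that centre, and preferably school-size category within centre, is a mandatory stratum or fixed effect in every aggregate-level between-arm comparison, including all aggregate logistic models, and is not left among the optional covariates. Use a centre-stratified test (Cochran-Mantel-Haenszel type for categorical outcomes, van Elteren type for ranks) or a model with centre fixed effects, in each case in a form that also accounts for the school as the randomised unit. Examples are a school random effect, a cluster-adjusted stratified test, or a stratified analysis of school-level summaries. Keep the pooled unstratified tests as descriptive only.

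The cost is a change of wording in the analysis section. Centre and size category are already known from the randomisation, and no further pupils or data are needed.
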